## Abstract

**Background:**

Hand osteoarthritis (OA) is a prevalent joint disorder and a great burden to both patients and society. While electroacupuncture (EA) and topical diclofenac sodium gel (DSG) are both currently used to treat OA, no head-to-head study of EA and topical DSG for hand OA exists. Thus, it remains unknown whether one intervention offers improved outcomes over the other. This study aims to compare the effects of EA and topical DSG in patients with hand OA.

**Methods:**

A total of 108 participants with hand OA according to the American College of Rheumatology criteria will be recruited and randomly assigned to the EA group or topical DSG group with a 1:1 allocation ratio. Participants in the EA group will receive EA treatment thrice weekly for 4 weeks, followed by a 12-week follow-up. In the topical DSG group, topical DSG at a dose of 2 g over the affected joints per hand will be applied four times per day for 4 weeks. The outcomes will be measured at weeks 4, 8, and 16. The primary outcome will be the change in average overall finger joint pain intensity in the dominant hand from baseline to week 4. All outcome variables will be analyzed on an intention-to-treat principle. All statistical tests will be two-sided.

**Discussion:**

This study will help determine which of the two treatment protocols, EA or topical DSG, is more effective for the clinical treatment of hand OA.

*Trial registration* ClinicalTrials.gov identifier: NCT04402047. Registered 16 May 2020, https://clinicaltrials.gov/ct2/show/NCT04402047

## Introduction

Hand osteoarthritis (OA) is a prevalent joint disorder characterized by pain, stiffness, and bony enlargements/swellings of multiple joints, in particular the distal interphalangeal (DIP), proximal interphalangeal (PIP), and first carpometacarpal (CMC) joints [1, 2]. Symptomatic hand OA is estimated to affect 15.9% of women and 8.2% of men in the general population [3] with a variable disease course [4], occurring more frequently in the elderly [3, 5]. The exact pathogenesis of hand OA is unknown but likely to be multifactorial [6]. Clinically, hand OA can be categorized into the following subsets: erosive, thumb-based, interphalangeal joint (with or without nodes) OA and generalized hand OA [7]. In addition to pain and stiffness, patients with hand OA often suffer from reduced grip and pinch strength, decreased range of motion in the involved and noninvolved joints [8], and difficulty performing dexterous tasks [9], resulting in disability in activities of daily living and considerable frustration [10].

At present, few therapeutic options with proven effectiveness are available for hand OA [11]. The effects of non-pharmacologic approaches are modest, and non-steroidal anti-inflammatory drugs (NSAIDs) are commonly used in the pharmacological treatment of patients with hand OA. Because topical NSAIDs have equivalent efficacy and a lower frequency of adverse events (AEs) compared with oral NSAIDs [12, 13], topical NSAIDs have been recommended as the preferred treatment option [14] Diclofenac sodium gel (DSG) is one of the commonly used topical NSAIDs, and studies have shown that it can provide local pain relief for patients with hand OA with reduced systemic exposure [15, 16], potentially reducing the risk of AE. However, the modest efficacy of NSAIDs is challenging for clinicians, and alternative effective therapies are still needed.

Acupuncture is an ancient Chinese therapy that provides beneficial effects. It is effective in a host of pain-related conditions, ranging from low back pain, neck pain, shoulder pain, and migraine to pain from knee OA [17]. The exact mechanisms of the analgesic effects of acupuncture are complex and have been thought to involve endogenous opioid release [18]. At present, there is a considerable amount of research demonstrating the positive effects of acupuncture on pain and function in knee OA [19]. Although hand OA is among the most prevalent OA phenotypes [20], the research on the effects of acupuncture in people with hand OA is very limited.

We have designed this pragmatic randomized trial to investigate the clinical effectiveness and safety of 4-week electroacupuncture (EA) therapy compared to topical DSG for the treatment of hand OA. Our primary hypothesis is that EA will provide greater relief from pain in patients with hand OA compared with topical DSG.

## Methods and design

### Study design

This will be a parallel-design, assessor-blinded, randomized trial with a 1:1 allocation rate. The study is designed to adhere to the standard protocol items including the Recommendations for Interventional Trials [21] and the Standards for Reporting Interventions in Clinical Trials of Acupuncture [22] guidelines. The study flow diagram and treatment schedule are presented in Figs. 1 and 2.

**Fig. 1 Fig1:**
[figure not shown]
Study flow diagram

**Fig. 2 Fig2:**
[figure not shown]
Study schedule

### Study setting and recruitment

This trial will be conducted at Guang’anmen Hospital, China Academy of Chinese Medical Sciences, and Yantai Hospital of Traditional Chinese Medicine from August 2020 to August 2022. A total of 108 participants will be publicly recruited through the use of posters and hospital websites. The duration of the trial for each participant will be 17 weeks: 1-week baseline, 4-week treatment, and 12-week follow-up.

### Randomization and blinding

Participants will be randomized to the EA group or topical DSG group at a ratio of 1:1 using a fixed block randomization (block size *n* = 4). The randomization schedule will be generated with PROC PLAN of SAS 9.4 (SAS Institute Inc., Cary, NC, USA) by the study biostatistician. To help conceal the details of the group allocation, consecutively numbered and sealed opaque envelopes prepared by an independent staff member will be used. After the participant has completed all the baseline measurements, the envelopes will be opened in sequence by a research coordinator who will be not involved in treatment and outcome assessments.

The outcome assessor and data manager will be blinded to the group assignments and not involved in providing the interventions. Allocation will be revealed to the researchers (including acupuncturists) delivering the intervention, but participants will be asked to not disclose details about their group allocation with the outcome assessors.

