The strengths of the trial include the strict inclusion and exclusion criteria, measurement of outcomes recommended by the OMERACT-OARSI, and blinding of the outcome assessor and data manager. We acknowledge several limitations exist in this trial. First, although this study could provide clinically relevant data important for patients with hand OA and the clinicians who treat them, the absence of a comparator group treated with placebo will make it difficult to exclude non-specific physiological responses to acupuncture. Second, we will be not able to blind participants and acupuncturists, which could potentially introduce bias in the results. Third, although symptomatic improvement may occur secondary to structural benefit, we will not use hand imaging assessments, because we do not expect our treatment to bring a structural change in the short term. Fourth, topical DSG will be used four times daily in our study based on evidence from previous literature [15, 41] and clinical experience. However, it may lead to a relatively poor compliance for patients, and result in a certain compliance bias. Fifth, considering the forces acting on the first CMC joint may much higher than that on the DIP and PIP joints in daily life, the comparison of the numbers of joints involved between patients would bring bias; the result will be interpreted as exploratory and viewed with caution. Sixth, the fixed acupuncture regimen will be used in this study; however, whether different acupuncture doses or different acupoints will show different benefits for patients should be evaluated in future studies.

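### A fixed, disclosed block of 4 with unblinded treating staff lets anyone who can follow the allocation sequence know up to one third of allocations in advance

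*Protocol article*

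**What the plan says.** Under Randomization and blinding, the Protocol article specifies allocation "at a ratio of 1:1 using a fixed block randomization", with a block size of 4 and the schedule generated in SAS by the study biostatistician. On concealment it states that "consecutively numbered and sealed opaque envelopes prepared by an independent staff member will be used". Once baseline measurements are complete, "the envelopes will be opened in sequence by a research coordinator who will be not involved in treatment and outcome assessments". On blinding it states: "Allocation will be revealed to the researchers (including acupuncturists) delivering the intervention".

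Study design describes the trial as assessor-blinded, and the Discussion concedes that "we will be not able to blind participants and acupuncturists". Study setting and recruitment names two hospitals, Guang'anmen Hospital of the "China Academy of Chinese Medical Sciences, and Yantai Hospital of Traditional Chinese Medicine". The article does not say whether each hospital has its own list or envelope series. It also does not say whether the coordinator or the treating staff may take part in recruitment or screening.

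**The concern.** Sealed opaque envelopes hide the content of the next envelope. They do not hide what the previous envelopes imply. With one known block size of 4 and equal allocation, two participants in one arm within a block settle the rest of that block, and the fourth place is always settled. Sequential numbering helps a reader of the sequence to locate the block boundaries.

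The coordinator sees every arm that he or she opens, and the treating staff are told the arms of the people they treat. The coordinator is kept out of treatment and outcome assessment only; nothing in the article keeps the coordinator or the treating staff out of recruitment or screening.

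At stake is selection at enrolment. Some eligibility criteria need judgement, such as whether an upper-limb pain syndrome could disturb the rating of hand pain, or whether a person can comply. The timing of enrolment also decides which envelope a person receives. Foreknowledge of the arm could influence either. The primary outcome is a self-reported pain VAS in unblinded participants, and the planned difference is 7 points with an SD of 12, so modest differences between the people entering each arm would matter. Blinding the assessor acts after randomization and does not protect this step.

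**Working it through.** **Inputs.** From Randomization and blinding: ratio 1:1, block size 4. From Sample size calculation: 108 participants, 54 per arm. The article gives no predictability figure to reproduce; 108 is used only to turn a share into a count. It does reproduce: a two-sided t-test for 7 points with SD 12 at 80% power needs 48 per arm, and 48/0.90 = 53.3, rounded up to 54 per arm. The number of blocks is 108/4 = 27.

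**1. Certain allocations with full sight of the sequence.** There are 6 equally likely blocks. AABB and BBAA leave 2 forced places each; ABAB, ABBA, BAAB and BABA leave 1 each.

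- Mean per block: (2×2 + 4×1)/6 = 8/6 = 1.333
- Share: 1.333/4 = 33.3%
- Expected count: 27 × 1.333 = 36 of 108
- Possible range: 27 × 1 = 27 to 27 × 2 = 54

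**2. Best-guess rate with full sight.** The guesser always names the arm with more places left.

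- Place 1: 1/2
- Place 2: 2/3
- Place 3: (1/3)×1 + (2/3)×(1/2) = 2/3
- Place 4: 1
- Mean: (0.500 + 0.667 + 0.667 + 1.000)/4 = 2.833/4 = 70.8%, against 50% by chance

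**3. One list interleaved between the two hospitals.** Assume that each envelope goes to a given hospital with probability p, that staff know the envelope numbers, and that they see only their own site's allocations. A place is certain when both places of one arm have already been used at that site.

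- Place 3: p² × 1/3
- Place 4: p² × 1, because the first three places always contain two of one arm
- Site share: (p²/3 + p²)/4 = p²/3
- Overall share with q = 1 − p: (p³ + q³)/3

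| Assumed split | Larger site | Smaller site | Overall |
|---|---|---|---|
| 50:50 | 8.3% | 8.3% | 8.3% |
| 70:30 | 16.3% | 3.0% | 12.3% |
| 90:10 | 27.0% | 0.3% | 24.3% |

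A simulation gave the same overall shares: 8.3%, 12.3% and 24.4%. The splits are assumptions, because the article gives none. With a separate list, or whole blocks, for each hospital, p = 1 and the share returns to one third.

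**4. Alternatives.** The observer has full sight of the list. For varying sizes, each size is equally likely and the observer knows the set of sizes but not their order (simulated).

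| Scheme | Certain | Best guess correct |
|---|---|---|
| Fixed 4 | 33.3% | 70.8% |
| Fixed 6 | 25.0% | 68.3% |
| Fixed 8 | 20.0% | 66.6% |
| Random 4 and 6 | about 5.6% | 69.2% |
| Random 4, 6 and 8 | about 2.3% | 67.9% |

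For blocks of 4 and 6, 5.6% of 108 is about 6 allocations.

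**The case against.** The strongest reply is that the conditions for one third are not shown to be met. Allocation is revealed to those delivering treatment, not to all staff. Eligibility is decided by a rheumatologist or hand surgeon, and nothing says these doctors learn earlier allocations. Envelopes are opened only after baseline, by someone outside treatment and outcome assessment. Several entry criteria are numeric or laboratory-based: pain of at least 40 mm, a rise of at least 20 mm during washout, radiographic grade and negative serology. The documents also do not show whether the block size was public while participants were being enrolled. All of this stands. It makes the one third an upper figure conditional on access, and the bias a possibility. It does not remove the weakness, because the coordinator necessarily sees the arms that he or she opens and some eligibility judgement remains.

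A reader might also infer that randomization is not stratified by hospital, so that hospital and treatment may be confounded and hospital must enter the analysis model. The article does not support this. It is silent on stratification, and a condensed article may leave that to the full protocol. Nor would a missing stratification produce the one third: a single list shared by two hospitals lowers what staff at one site can deduce.

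Finally, a reader might call the trial fully open-label. It is unblinded for participants and treating staff, but the outcome assessor and data manager are blinded.

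**Conclusion.** The point holds as a conditional weakness in a choice that the article makes explicitly. A full sequence observer who knows the block boundaries can foresee an expected 36 of 108 allocations. Under one interleaved list with each site seeing only its own allocations, the share is about 8% to 24% over the assumed splits. Which case applies depends on how the list is divided and on who takes part in screening, and the article settles neither. No selection bias has been shown to have occurred. This is an improvement worth making because it is cheap, not a fault that invalidates the comparison.

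**What to change.** For all envelopes not yet opened, replace the fixed block of 4 with randomly varying block sizes, for example 4 and 6. Keep the sizes in a document that recruiting and treating staff cannot see.

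The cost is a new run of the schedule program and new envelopes. There are two downsides. The best-guess rate barely moves, from 70.8% to about 69%, so the gain is in removing certainty rather than in restoring chance-level guessing. The final imbalance can also be slightly larger: at most 3 per list when a block of 6 is left incomplete, against at most 2 with blocks of 4.

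If all envelopes have been opened, report predictable allocation as a limitation alongside those in the Discussion, and compare baseline characteristics of forced and unforced allocations by arm. With about 36 forced allocations expected, or 18 per arm, that comparison can reveal only large differences, and a clean result would not rule out selection.

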### Participants

Participants will be considered eligible by a rheumatologist or hand surgeon if they fulfill the American College of Rheumatology (ACR) [23] clinical classification criteria for the diagnosis of hand OA in dominant (target) hand. The criteria are as follows: hand pain, aching or stiffness, and 3 or 4 of the following features: hard tissue enlargement of at least two of 10 selected joints (the 2nd and 3rd DIP and PIP joint and first CMC joint of both hands), hard tissue enlargement of at least two DIP joints, swelling of fewer than three metacarpophalangeal joints, and deformity of at least one of the 10 aforementioned selected joints. For inclusion, they must meet all of the following inclusion criteria and not fulfill any of the exclusion criteria.

### Inclusion criteria

Age ≥ 18 years and ≤ 80 years;History of hand OA for at least 3 months before enrollment;Reported an average overall finger joint pain intensity in the dominant hand over the past 48 h of at least 40 mm according to a 100-mm visual analog scale (VAS, 0 = no pain, 100 = maximal pain). Patients applying NSAIDs at the screening must have an increase in pain in the dominant hand of ≥ 20 mm during washout;Posterior–anterior radiographs show Kellgren–Lawrence grade 1, 2, or 3 changes [24] in symptomatic joints;Tests for rheumatoid factor and anticyclonic citrullinated peptide are negative to exclude inflammatory arthritis;Ability to comply with the study protocol, understand the medical information form, and provide written informed consent.

### Exclusion criteria

History or current evidence of secondary OA (due to causes other than a solely degenerative joint disease) or symptomatic OA at additional locations besides the hand(s) requiring treatment, or any painful syndrome of the upper limb, which may interfere with evaluation of hand pain;History of inflammatory arthritis (e.g., rheumatoid arthritis [RA], psoriatic arthritis), hemochromatosis, metabolic, or neuropathic arthropathies;History of trauma, dislocation, or operation to the hand or arm in the previous 3 months;Hand pain and stiffness due to tissue scarring or tendinitis;Skin damage or serious skin disorders in the hands;Intake of antidepressants, anticonvulsants, vascular drugs, or narcotics during the 10 days prior to beginning the study;Oral, intramuscular, intra-articular, or intravenous corticosteroids or hyaluronic acid injection within 3 months preceding enrollment;Serious uncontrolled medical conditions such as cancer, uncontrolled cardiovascular disorder, severe hepatic/renal insufficiency, or coagulation disorder;Known allergy, contraindication, or intolerance to diclofenac, acetaminophen, or gel components;Known phobia to acupuncture or having received acupuncture treatment within 4 weeks prior to enrollment.

### Interventions

#### EA group

The EA protocol was determined according to the meridian theory of TCM and the consensus of three senior doctors of TCM who have more than 30 years’ clinical experience. The acupuncturists who will perform the interventions will be state-licensed and have more than 2 years’ practical experience.

We will apply Ashi points (the most obvious tender points over the affected joints), Baxie points (Ex-UE9, 4 points proximal to the margin of the webs between each two of the five fingers of a hand), Houxi (SI3), and Waiguan (TE5) in this trial. The location of the above acupoints will be based on the nomenclature and location of acupuncture points drafted by the National Standard of the People’s Republic of China (GB/T 12 346-2006) [25]. Sterile single-use stainless steel needles (size 0.3 mm × 40 mm) and the SDZ-V EA apparatus (all Hwato brand, Suzhou Medical Appliance Factory, Suzhou, China) will be utilized. After local skin disinfection with 75% alcohol wipes while patients are in a sitting or supine position, acupuncturists will insert needles perpendicularly into the Ashi points to a depth of approximately 2–3 mm until they pierce the bone surface; horizontally into the Baxie points toward the wrist to a depth of 5–10 mm; and perpendicularly into SI3 and TE5 to a depth of approximately 5–10 mm. The depth of needling will vary based on the participant’s body sizes. After insertion, all needles except those in the Ashi points will be manually manipulated to achieve De qi sensation, which is defined as a composite of unique needling sensations, including soreness, numbness, distention, or heaviness felt by both participants and acupuncturists [26]. Thereafter, the needles at Baxie 1 (between thumb and index fingers) and Baxie 4 (between the ring finger and little finger) will be connected using alligator clips from the EA apparatus. The electrical stimulation will last for 30 min with a continuous wave of 10 Hz and a fixed current intensity of 0.5–2 mA according to the participants’ sensitivity. All the needles will be retained for 30 min and then gently removed.

Participants will undergo EA treatment three times per week for a total of 12 sessions in 4 consecutive weeks.

#### Topical DSG group

Participants will be shown how to apply the topical DSG (Mayinglong Pharmaceutical Group Co., Ltd., Hubei, China; 100 mg of diclofenac sodium per gram of gel, 20 g in each tube; H19990010) under supervision and will be provided with detailed instructions for the use and application of the gel as well as dosing pads to standardize the application amount. The gel will be gently rubbed over the affected joints without excessive joint movement four times per day for 4 weeks, and participants will be asked not to wash their hands for 1 h after application. Each hand treatment will be used in identical dispensing doses of gel (4-cm strip, approximately 2 g, which was judged sufficient for approximately half the surface of each hand [200 cm^2^] [15]). Dosing times should be distributed evenly over waking hours.

If bilateral hands are affected, both sides will be treated. The value in the dominant hand or both hands will be used in the analysis according to the requirements of different outcome measurements.

### Rescue medication

Only acetaminophen (500 mg/T, Tianjin Smith Kline & French Laboratories Ltd., Tianjin, China) will be allowed to a maximum dose of 2 g daily for up to 3 days as rescue medication if insufferable pain occurs. Participants will not be allowed to take rescue medication within 60 h before the baseline and outcome measurements. If a participant takes rescue medication within the prohibited time during the treatment and follow-up period, the assessor will postpone the outcome measurement visit.

### Outcome measures

#### Primary outcome

The primary outcome in this trial is the change in average overall finger joint pain intensity in the dominant hand over the previous 48 h, measured on a 0–100 VAS (0 = no pain, 100 = maximal pain) from baseline to week 4. The changes at week 8 and week 16 from baseline also will be assessed.

#### Secondary outcomes

The secondary outcomes are as follows:The proportion of participants achieving at least a 15-point reduction in average overall finger joint pain intensity in the dominant hand from baseline to weeks 4, 8, and 16: As previously described, 15 of 100 mm for absolute improvement could reflect a minimum clinically important improvement in pain for patients experiencing hand OA [27].Change in Australian Canadian Osteoarthritis Hand Index (AUSCAN) total score, and pain, stiffness, and physical function subscales from baseline to weeks 4, 8, and 16: The AUSCAN index contains a 15-item scale referring to hand pain (5 items), stiffness (1 item), and function (9 items) during the preceding 48 h [28], which is valid, reliable, and responsive in patients with hand OA [29]. All items are scaled on a 0–100 VAS (0 = none to 100 = very severe), with higher scores indicating more severe symptoms/functional impairment. The AUSCAN functional assessments will be performed for the dominant hand only. The total AUSCAN score will be calculated as the average of scores on 15 questions [29].Change in Functional Index for HOA (FIHOA) [30] from baseline to weeks 4, 8, and 16: The FIHOA is a patient-reported hand function questionnaire, comprising 10 items with a total score is calculated, ranging from 0–30 (0 = best activity performance, 30 = very poor activity performance).Change in the number of self-reported painful joints and painful joints at digital pressure and swollen joints from baseline to weeks 4, 8, and 16.Change in hand grip strength and pinch strength of the fingers from baseline to weeks 4, 8, and 16: Hand grip strength and pinch strength of the fingers of the dominant hand will be tested using a hand dynamometer (KYTO 2324, Kangdu Electronic Manufacture Co. Ltd, Dongguan, China) and a Jamar digital pinch gauge (Allegro Medical, Illinois, USA), respectively. Grip strength will be measured first, followed by pinch strength of the fingers, including palmar (three-jaw chuck) pinch, key (lateral) pinch, and tip (two-point) pinch [31]. For each of the tests, the participants will be in a standing position with the shoulder adducted and neutrally rotated and the elbow slightly extended [32]. Participants will conduct three trials, with an interval of 30 s at a minimum between each trial. The final score for analysis will be recorded in kilograms, and the average of the three consecutive values measured.Change in patient global assessment of improvement [33] from baseline to weeks 4, 8, and 16: The patients will be asked to respond to the question “Considering all the ways your hand OA affects you, how have you been during the last 48 h?” [34] on a self-administered 0–100 VAS (0, worst possible, to 100, best possible, in 10-point increments) at 4, 8, and 16 weeks.The proportion of responders according to the Outcome Measures in Rheumatological Clinical Trials (OMERACT) and Osteoarthritis Research Society International (OARSI) responder criteria [35] at weeks 4, 8, and 16: The OMERACT-OARSI response is defined as an improvement in either pain (0–100 overall finger joint pain) or function (0–100 AUSCAN physical function) by ≥ 50% (relative) and ≥ 20/100 (absolute); or an improvement of ≥ 20% (relative) and ≥ 10/100 (absolute) in ≥ 2 of the following: pain, functioning, and patient global assessment of improvement.Change in quality of life assessed by the World Health Organization Quality of Life abbreviated version (WHOQOL-BREF) from baseline to weeks 4, 8, and 16: The WHOQOL-BREF is a 26-item self-report questionnaire rated on a 5-point Likert-type scale with four domains of QOL: physical (7 items), psychological (6 items), social (3 items), and environment (8 items), plus two items representing the general QOL [36]. The four domain scores are scaled in a positive direction with higher scores indicating a higher QOL. In this trial, we will use the Chinese version of the WHOQOL-BREF, which has been reported to have adequate reliability and validity [37].Participants’ expectations for acupuncture at baseline: At baseline, participants in the EA group will be asked to answer the following question: “What level of improvement do you expect from EA for your hand OA?” Participants can choose one of the following five answers: “extreme improvement,” “moderate improvement,” “slight improvement,” “no improvement,” or “unclear.”Self-reported consumption of acetaminophen for hand OA during weeks 1–4 and weeks 5–12: the proportion of participants using acetaminophen and the average dosage of acetaminophen used weekly will be calculated and assessed.

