#### Sample size calculation

This trial hypothesizes that 4 weeks of EA treatment will be superior to topical DSG in terms of pain relief in the dominant hand for patients with hand OA. Based on the results of a previous study [15], the OA pain intensity in the dominant hand on the 0–100 VAS scale was reduced by an average of 31.1 points in the topical DSG group and 23.9 points in the vehicle group. We predict that EA will display superiority over topical DSG by at least a 7-point better relative reduction in VAS score with a standard deviation of 12. Assuming a two-tailed test with a possible drop-out of 10% of the patients, a total of 108 patients (54 in the EA group and 54 in the topical DSG group) will be required for 80% power on a 5% alpha level.

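### The acetaminophen-use outcome is defined only to week 12, although follow-up and outcome visits run to week 16, so it omits weeks 13–16

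*Protocol article*

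**What the plan says.** The last item under Secondary outcomes is "Self-reported consumption of acetaminophen for hand OA during weeks 1–4 and weeks 5–12". For these windows, "the proportion of participants using acetaminophen and the average dosage of acetaminophen used weekly will be calculated and assessed".

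Study setting and recruitment gives each participant "1-week baseline, 4-week treatment, and 12-week follow-up", 17 weeks in all. The Methods part of the Abstract states: "The outcomes will be measured at weeks 4, 8, and 16". For the pain score, Primary outcome adds: "The changes at week 8 and week 16 from baseline also will be assessed". Every other efficacy outcome measured after baseline is also taken to week 16.

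Under Rescue medication, acetaminophen is the only drug allowed, and it is barred in the 60 hours before baseline and outcome measurements. The rule extends past treatment: "If a participant takes rescue medication within the prohibited time during the treatment and follow-up period, the assessor will postpone the outcome measurement visit".

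**The concern.** The first acetaminophen window matches the treatment period exactly. The second starts where follow-up starts but stops four weeks before follow-up ends, and no reason is given. The article states the window outright and it does not fit the timeline in the same article, so this is not a detail left to an analysis plan.

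Both treatments end at week 4, and participants know which one they received. The week-16 results are there to show whether any difference between arms lasts. Rescue use in the preceding weeks is part of that picture: similar pain scores mean something different if one arm reached them with more analgesic. Rescue use in weeks 13–16 is contemplated by the protocol, but no defined outcome summarises it.

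**Working it through.** The check is a count of weeks. The sample size rests on the week-4 change in pain and does not enter.

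**Inputs**
- Baseline 1 week, treatment 4 weeks, follow-up 12 weeks (Study setting and recruitment).
- Outcome visits at weeks 4, 8 and 16 (Abstract, Methods; repeated for the individual outcomes).
- Acetaminophen windows: weeks 1–4 and weeks 5–12 (Secondary outcomes).
- Recall for the pain score: 48 hours (Primary outcome). Ban on rescue medication before a measurement: 60 hours (Rescue medication).

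**Step 1. Reproduce the plan's own timeline.** 1 + 4 + 12 = 17 weeks, as stated. Counted from the start of treatment, 4 + 12 = 16, which agrees with the last visit at week 16. Follow-up is therefore weeks 5–16, which is 16 − 5 + 1 = 12 weeks.

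**Step 2. Compare the windows.**

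| Period | Timeline | Acetaminophen outcome | Not covered |
|---|---|---|---|
| Treatment | weeks 1–4 (4 weeks) | weeks 1–4 (4 weeks) | none |
| Follow-up | weeks 5–16 (12 weeks) | weeks 5–12 (12 − 5 + 1 = 8 weeks) | weeks 13–16 (12 − 8 = 4 weeks) |

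Share of follow-up omitted: 4/12 = 33%. Share of the post-randomisation period omitted: 4/16 = 25%.

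**Step 3. Fit to the visits.** Week 12 is not a listed visit. At the listed visits, use in weeks 9–12 could be reported only at week 16, and participants would have to separate it from weeks 13–16 by memory. The only diary described (Quality control) is for gel use, in the gel arm.

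**Step 4. How far could the uncounted use act on the week-16 scores?** The ban exceeds the pain recall by 60 − 48 = 12 hours. If it is followed, no acetaminophen is taken inside the period that the week-16 pain score rates. The same holds for the AUSCAN index and the patient global assessment, which also refer to 48 hours. The article states no recall period for the FIHOA or the quality-of-life questionnaire, so this argument cannot be carried over to them.

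**The case against.** The strongest case on the other side has four parts.

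- **The week-16 scores are already protected.** A reader might infer that they cannot be interpreted without rescue data for weeks 13–16. The article does not support this. The 60-hour ban applies in follow-up, applies to both arms, and outlasts the 48-hour recall. This stands. What the rule does not do is record or compare use over the four weeks, which is the purpose of the outcome.
- **The summaries would not be wrong.** One might say that the follow-up figures for users and weekly dose will be in error. But the item never calls weeks 5–12 the follow-up period. A proportion and a weekly average for weeks 5–12 are correct for that window and incomplete for the whole of follow-up. A 1.5-fold error (12/8) would arise only if use over all 12 weeks were divided by 8, and nothing says that it will be. This stands.
- **The data may still be collected.** The item says what will be calculated, not what will be recorded. The study schedule (Fig. 2), the full protocol and the case report form were not available here, and staff must in any case learn of very recent use before the week-16 visit. So it cannot be said that the data go uncollected. The published definition would still exclude them.
- **The shorter window may be intended.** It could be deliberate for a descriptive outcome. The article neither says so nor rules it out, and the absence of a week-12 visit points to a slip without proving one.

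**Conclusion.** The mismatch is real and its severity is minor. As written, the outcome omits weeks 13–16, 33% of follow-up and 25% of the post-randomisation period, and ends between visits. The comparison of rescue use is therefore incomplete for the month before the last assessment, and the reading of durability at week 16 is incomplete to that extent.

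The week-4 primary outcome, its analysis and the sample size are untouched, and weeks 1–4 are fully covered. The conclusion assumes that study weeks are counted from the start of treatment, as the week-16 final visit implies, and that no document not seen here defines the window differently.

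**What to change.** Reconcile the acetaminophen item under Secondary outcomes with the timeline in the Abstract and in Study setting and recruitment. Define the second window as weeks 5–16, or split it into weeks 5–8 and 9–16 so that each window closes at a visit, and collect the self-report at the existing week-8 and week-16 visits. Use the number of weeks in each window as the divisor for the weekly average. If the stop at week 12 was intended, say so and give the reason.

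This is a one-line change to the outcome definition, with a matching change to the case report form if that form follows the present wording. It needs no new visit, no change to the rescue rule and no change in sample size. The downside is that the report at week 16 would cover eight weeks of recall (weeks 9–16). That is longer than now only if use up to week 12 is gathered at some contact that the article does not mention.
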